#### Validation study

A power calculation, using Python, identified that we will need to screen 268 people with ‘possible’ psychosis to identify 162 ‘true positives’ to have at least 80% power (alpha 0.05) to detect a change percent value of specificity of the diagnostic tool from 80% to 90%. Initial case-finding of people with ‘possible’ psychosis will result from awareness-raising in the community and from training HSAs. People with possible psychosis will then be assessed by HSAs using the screening tool. All people who are considered to have psychosis based on the screening assessment (‘probable’ psychosis) and a random sample of screen negatives will undergo the gold standard diagnostic assessment administered by the RAs. The RAs will be masked to the outcome of the screening test. The gold standard diagnosis will include any diagnosis within the ‘schizophrenia or other primary psychotic disorders’ section of ICD-11, and affective psychosis, but will exclude organic or substance-induced psychoses. We will investigate sensitivity, specificity, positive and negative predictive values. The key concerns are to minimise false positives of a definitive psychosis diagnosis and to detect those with ongoing (not brief) psychosis that would benefit from an intervention that can be provided. We will use multivariate analyses to investigate possible predictors of inaccurate diagnosis (e.g. gender, educational level, age) to inform further implementation.

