#### Activities

The key activities in WP3 will be to pilot the prototype manual and procedures of the psychosis detection and management system to N = 268 people to identify an anticipated N = 150 who screen positive for psychosis. This will be carried out sequentially, district by district, in the two districts involved in WPs 1 and 2 (Salima and Chiradzulu) and a third district (Ntcheu), which is equidistant between the others. The key informants in this WP are PWLE and their families, formal and informal caregivers, traditional and religious healers, HSAs, and clinic staff in Primary Health Centre and District Mental Health Teams. A process of engagement needs to be developed in the new Ntcheu district involved in WP3. This will be completed through ToC 6 workshop with PWLE and their families, and the other stakeholders above. Table 3 below gives an overview of WP3 activities.

**Table 3 pone.0293370.t003:** WP3 piloting of the psychosis detection and management system in 3 districts.

**Research questions**	**Methods**	**Key informants/participants**	
		**Community**	**Healthcare**
*What are the contextual adaptations required to implement the psychosis detection and management system in Ntcheu*?	ToC workshop 6 (n = 20 in Ntcheu)	People with lived experience Family/caregivers Traditional Healers Religious Healers	HSAs PHC staff DMHT staff Government Rep
*To what extent can HSAs trained in the psychosis and management tool accurately detect and refer people with psychosis to further care*?	Validation study (n = 268 screened)	People with possible psychosis	**-**
*Can the psychosis detection and management tool be delivered with fidelity by HSAs*?	Fidelity assessment (n = 60)	-	HSAs
*How did people with psychosis experience the detection and management process and what are the views of their diagnosis*	Qualitative interviews (n = 20 across three districts)	People with psychosis	-
*How did HSAs experience the detection and management process*? *How have their views on people with psychosis have changed*?	Qualitative interviews (n = 20 across Salima and Ntcheu)	-	HSAs
*What is the impact of the psychosis management and detection tool on service utilisation*?	Review of district health data	-	-

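### The validation study's 80% power for specificity is attached to 162 true positives, who do not enter specificity and who outnumber the 150 people expected to screen positive

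*Protocol article*

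**What the plan says.** All of this is in the protocol article, under WP3.

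- **Validation study, size:** 268 people with possible psychosis are to be screened. The stated target is "162 ‘true positives’ to have at least 80% power (alpha 0.05) to detect a change percent value of specificity of the diagnostic tool". The null value is 80% and the alternative 90%.
- **Activities, expected yield:** the pilot goes to "N = 268 people to identify an anticipated N = 150 who screen positive for psychosis". Table 3 repeats 268 as the number screened in the validation study.
- **Validation study, verification:** everyone who screens positive has the gold-standard interview, but only "a random sample of screen negatives will undergo the gold standard diagnostic assessment administered by the RAs". The size of that sample is not given.
- **Validation study, priority:** "The key concerns are to minimise false positives of a definitive psychosis diagnosis".

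The article gives no required number of people without psychosis, no assumed share of cases among the 268, and does not say whether alpha is one- or two-sided.

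**The concern.** Specificity is TN/(TN + FP), where TN is true negatives and FP false positives. Both groups consist of people without psychosis. A true positive is in neither, so a count of true positives cannot carry power for specificity. The article states its power basis and attaches it to the wrong group, so this is not a detail left to another document.

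The count also conflicts with WP3 Activities. True positives are a subset of screen positives, so 162 of them cannot be found among 150.

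At stake is the measure that answers the study's stated priority on false positives. Participants enter because psychosis is already suspected, so a high case share is plausible. With no required number of non-cases stated, a shortfall in that group would not show against the figures given.

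**Working it through.** **Inputs.** From the article: 268 screened, 162 true positives, 150 screen positives, specificity 80% (p0) against 90% (p1), power 80%, alpha 0.05. Assumed: a one-sample test, two-sided alpha, and the case shares and sensitivities named below.

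**1. Reproducing 268.** For a one-sample test of a proportion,

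n = [z(0.975)·√(p0(1−p0)) + z(0.80)·√(p1(1−p1))]² / (p1−p0)²

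= (1.960 × 0.4 + 0.8416 × 0.3)² / 0.01 = (0.7840 + 0.2525)² / 0.01 = 107.4 people without psychosis.

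If 60% of those screened are cases, 107.4 / 0.40 = 268.6, which agrees with 268, and 0.60 × 268 = 160.8, close to 162. So 268 is consistent with a specificity calculation in which about 162 is the by-product number of cases.

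**2. Could 162 be the informative sample?** Power = Φ[(0.10√n − 0.7840)/0.3]. At n = 162 this is Φ(1.63) = 94.8%, not 80%. Other standard formulas at 80% power do not give 162 either: 83 (one-sided), 118 (continuity-corrected), 98 (arcsine), 199 per group (two-sample). The nearest is a one-sided two-sample test at 157 per group, which would still count non-cases.

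**3. Power in the plan's own remainder.** 268 − 162 = 106 non-cases.

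| Non-cases | Normal approximation | Exact binomial, upper tail ≤ 0.025 |
|---|---|---|
| 106 | 79.3% | 74.0% |
| 107 | 79.8% | 81.9% |
| 108 | 80.3% | 81.0% |
| 110 / 111 / 112 | 81.1 / 81.6 / 82.0% | 79.1 / 78.2 / 77.2% |
| 113 | 82.4% | 84.3% |

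Exact power stays at or above 80% at every n checked from 113 to 399.

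**4. The count of 162 against 150.** True positives cannot exceed 150, so the gap is at least 162 − 150 = 12 even with no false positives. If 162 means all gold-standard cases, 150 screen positives caps sensitivity at 150/162 = 92.6%. Screen positives would then be 162 × sensitivity + 106 × (1 − specificity). This is 150.8 at an assumed 80%/80%, and 140.2 at 80% sensitivity with 90% specificity.

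**5. Dependence on the case share, with 268 screened and all verified (assumed scenarios).**

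| Case share | Non-cases | Exact power |
|---|---|---|
| 50% | 134 | 88% |
| 60% | 107 | 82% |
| 70% | 80 | 59% |
| 75% | 67 | 49% |
| 80% | 54 | 36% |

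**6. Partial verification.** Of 106 non-cases, 84.8 screen negative at 80% specificity and 95.4 at 90%. If half the screen negatives are verified, the directly verified non-cases number 21.2 + 42.4 = 63.6, or 10.6 + 47.7 = 58.3. A plain exact binomial test on 64 or 58 people has power of 54% or 47%.

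Those figures describe the verified count only. An analysis that weights the verified negatives back up loses much less. Take 162 cases, 80% sensitivity (assumed) and 90% specificity: there are 95.4 + 32.4 = 127.8 screen negatives. Verifying half (63.9) adds a standard deviation of 127.8 × √(0.746 × 0.254 × 0.5 / 63.9) = 4.9 to the estimated TN. Multiplied by FP/106² = 10.6/11,236, that is 0.0046, against 0.0291 under full verification. A simulation gave about 3% more variance here and about 6% more at 80% specificity. Without weighting, the estimate is biased: 47.7/58.3 = 82% when the true specificity is 90%.

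**The case against.** The strongest reply is that this is a labelling slip and the design is sound. The required non-cases and the remainder of 106 agree to within two people, and 79.3% is 80% for planning purposes. That stands: neither 268 nor the 80% is shown to be wrong.

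Further points for the plan also stand:

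- The 74% at 106 reflects the stepwise behaviour of an exact test that the article does not name; one more person gives 82%. With one-sided alpha 0.05, exact power at 106 would be 89%.
- The 60% case share is inferred. By that route 268 − 107 = 161, not the printed 162, so it is a plausible reconstruction and not proof of how the figure arose.
- The 150 equals the WP4 sample size and may have been carried from there.

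A reader might also infer that recruitment stops at 162 cases, so that a high case share would end the study early with very few non-cases. The article does not support that. It fixes screening at 268, in the text and in Table 3, and contains no rule to stop or monitor on 162.

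None of this removes the two errors on the page: the power is attached to a group that does not enter specificity, and the stated count cannot be reached from the expected screen positives.

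**Conclusion.** The point holds as a mislabelled power basis and a contradiction between two sections of WP3. On the plan's own remainder of 106 non-cases the power is about 79% (normal approximation) or 74% (exact), provided all are verified and alpha is two-sided. The sample of 268 can stand.

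The practical weakness is that the power depends on two quantities the article does not state. One is the case share: above 60% power falls, to about 59% at 70% and 36% at 80%; below 60% it rises. The other is the fraction of screen negatives verified: half leaves about 58 to 64 directly verified non-cases, worth roughly 47% to 54% power in a plain exact test, with a much smaller loss if the analysis weights for the sampling. These are assumed scenarios, not forecasts. It would be wrong to conclude that the study is under-powered as designed.

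**What to change.** 1. In Validation study, replace 162 true positives as the basis of the power with the required number of people without psychosis, verified on the gold standard: about 108 by the normal approximation, or 113 if an exact test is used. State the test and whether alpha is two-sided.
2. State the assumed case share among those screened.
3. State how many screen negatives will be verified, sized to reach that number. If the verified negatives will be weighted back up, say so and give the power on that basis.
4. Relabel 162 as expected cases if that is what is meant. The authors should then reconcile it with the 150 in WP3 Activities, giving the sensitivity and specificity they assume.
5. If 268 stays fixed, restate the power over a range of case shares and verification fractions.

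The cost is mainly wording. No extra participants are needed if 268 is kept and the power restated. Verifying more screen negatives would add gold-standard interviews for the research assistants. Reaching 113 non-cases at a 60% case share would take 113/0.40 = 282.5, so 283 screened, 15 more than planned.

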## Introduction

Psychoses–principally schizophrenia and related conditions, including affective psychosis–can be experienced as deeply distressing and disabling conditions. Around 50% of people with psychosis in High Income Countries (HICs) will have ongoing symptoms and social and occupational functioning difficulties (APA, 2013). In one particularly comprehensive study, conducted in Finland, the combined lifetime risk of all psychoses was around 3%, with a prevalence of 1% [1]. The global point prevalence of schizophrenia is estimated to be 0.3–0.6% [2, 3].

Duration of untreated psychosis (DUP) is a key issue of clinical and public health concern. A longer DUP of even a few weeks or months has been consistently linked to worse outcomes in terms of more severe symptoms, worse social, vocational, and overall functioning, and reduced quality of life. This has been reported in many countries around the world, including low- and middle-income countries (LMICs) within Africa [4, 5]. The most cost-effective interventions for schizophrenia in Nigeria include community-based treatment with older antipsychotic drugs plus psychosocial support or case management [6]. Clinical trials indicate that antipsychotic drug treatment leads to quicker symptom relief, reduces the risk of relapse, and probably improves quality of life [7], and that psychosocial interventions such as illness education and support reduce relapse risk [8]. Notably, however, antipsychotic drugs can have unpleasant adverse effects which reduce their acceptability [9].

Malawi is a sub-Saharan African country with approximately 15 million people under the age of 30. No studies of the prevalence of psychosis generally or schizophrenia in Malawi have been conducted, but the increased risk of schizophrenia among the young and those living in poverty [10] are reasons to think it may be higher than in HICs. The prevalence of HIV/AIDS, malaria, and cannabis use [11, 12] could mean that organic and substance-induced psychoses are particularly common. Epidemiological surveys also suggest that brief psychoses could be more common in LMICs such as Nigeria than HICs [13].

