For establishing costs and consequences, data will be obtained at each of the data-collection points by asking patients (retrospectively) about service contacts, employment status, support from family and caregivers, and relevant personal expenditures (e.g. payments for services). We will compare these patient-reported service use patterns with data on impacts on service utilisation obtained from services themselves in WP3 to establish best possible estimates. Unit costs will be assigned to service utilisation data. These unit costs attached to service utilisation data will be drawn from extant sources and relevant previous research in Malawi, but it is likely that we will need to calculate most unit costs anew (for example, based on budget and salary information). In addition, we will use observations and questionnaires to establish the time that HSAs spend on the training and delivery of the intervention, and gather administrative data if needed. Lost productivity will be valued using data on employment disruption, earnings and care-giving or other household/community activities, applying human capital and opportunity costing approaches as appropriate; carer inputs will be valued on opportunity cost principles (including lost earnings).

To analyse the cost-effectiveness of the intervention, we will first calculate how costs change between baseline and follow-up: to show the resource consequences of the intervention across different budgets/sectors (healthcare, employment, individual households), and so inform judgements about future affordability. Cost-effectiveness analyses in this pre-post sequential group design will bring together the estimated costs and, in turn, data on the primary outcome (WHOQoL) and DALYs calculated from disability weights from the GBD/GHDx tool (http://ghdx.healthdata.org/gbd-results-tool). Incremental cost-effectiveness ratios will be computed under the assumption that baseline scores continue unchanged to follow-up, and that costs remain unchanged too. We will plot cost-effectiveness acceptability curves generated from bootstrap analyses. Discounting will not be needed as the evaluation does not extend beyond one year. Comparisons can be made with cost per DALY averted thresholds from [43] and other sources [44].

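### The validation study's reference standard counts brief psychosis as a case, although its stated aim is to detect ongoing, not brief, psychosis

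*Protocol article*

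**What the plan says.** The Validation study section defines the gold-standard diagnosis to "include any diagnosis within the ‘schizophrenia or other primary psychotic disorders’ section of ICD-11, and affective psychosis, but will exclude organic or substance-induced psychoses". It gives no criterion for duration or persistence, and none appears elsewhere in the article. Two sentences later it names the key concerns: to minimise false positives and "to detect those with ongoing (not brief) psychosis that would benefit from an intervention that can be provided". The study is powered on specificity, 80% against 90%, by screening 268 people and finding 162 described as true positives. Sensitivity and both predictive values will also be reported.

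The Introduction raises organic, substance-induced and brief psychoses as separate local considerations. On the last it says that "brief psychoses could be more common in LMICs such as Nigeria than HICs". The gold standard excludes the first two and does not mention the third.

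For WP4, the Economic analysis states: "Incremental cost-effectiveness ratios will be computed under the assumption that baseline scores continue unchanged to follow-up". It also plans sensitivity analyses that vary this counterfactual.

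**The concern.** A diagnostic accuracy study answers the question set by its reference standard. Here that standard is any primary or affective psychosis, while the stated purpose is ongoing psychosis. A brief episode that the tool flags is a true positive under the definition and a false positive under the aim. One that the tool correctly leaves unflagged is a false negative under the definition and a correct result under the aim. The tool could appear to meet its specificity target while missing it for the condition of interest, or be marked down for doing what was wanted.

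A second consequence is possible in WP4. If people with brief psychosis are among the screen positives who are followed up, some may recover unaided. With no control group, that recovery would be read as change after the intervention.

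**Working it through.** **Inputs.** From the Validation study: 268 screened, 162 cases, specificity 80% against 90%, at least 80% power, alpha 0.05. Assumed, because the documents give no figure: the brief share *b* of the 162 cases, how often brief cases are flagged (*f*), and the tool's sensitivity for ongoing psychosis (80% to 90%).

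**Step 1: the plan's own figure.** For a two-sided one-sample test of a proportion, the number of non-cases is

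n = [1.96·√(0.8·0.2) + 0.842·√(0.9·0.1)]² / 0.1² = (0.784 + 0.253)² / 0.01 ≈ 107.4.

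With 162/268 = 60.4% cases, taken as 60%, 107/0.40 = 267.5, so 268. The figure reproduces if 162 is read as the number with the reference diagnosis, leaving 268 − 162 = 106 non-cases. Approximate power at 106 is 79.3%. Everything below uses that reading and treats all 268 as classified. In practice only some screen negatives have the interview, so estimates would have to be weighted back.

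**Step 2: re-classify against ongoing psychosis.** Brief cases number B = 162·b and ongoing cases O = 162 − B. At an apparent specificity of 90%, false positives among non-cases are 0.10·106 = 10.6. With sensitivity *s* for ongoing psychosis:

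- Specificity for ongoing psychosis = 1 − (10.6 + f·B)/(106 + B)
- PPV for ongoing psychosis = s·O/(s·O + f·B + 10.6)
- Apparent PPV = (s·O + f·B)/(s·O + f·B + 10.6)
- Apparent sensitivity = (s·O + f·B)/162

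At b = 10%, B = 16.2 and O = 145.8:

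- f = 90%: 1 − (10.6 + 14.58)/122.2 = 79.4%
- f = 80%: 1 − (10.6 + 12.96)/122.2 = 80.7%
- f = 50%: 1 − (10.6 + 8.1)/122.2 = 84.7%

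With s = 90%:

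| Brief share (assumed) | Specificity, f = 50% | Specificity, f = 90% | PPV, f = 50% (apparent) | PPV, f = 90% (apparent) | Apparent sensitivity, f = 50% |
|---|---|---|---|---|---|
| 5% | 87.2% | 84.3% | 90.4% (93.1%) | 88.6% (93.2%) | 88.0% |
| 10% | 84.7% | 79.4% | 87.5% (92.9%) | 83.9% (93.2%) | 86.0% |
| 20% | 80.6% | 71.3% | 81.3% (92.6%) | 74.6% (93.2%) | 82.0% |
| 30% | 77.4% | 64.9% | 74.5% (92.3%) | 65.3% (93.2%) | 78.0% |

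With s = f = 80% and b = 10%, PPV is 116.64/140.2 = 83.2%, against an apparent 129.6/140.2 = 92.4%.

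**Step 3: direction.** Specificity is unchanged when f equals the false-positive rate of 10%: (10.6 + 1.62)/122.2 = 10.0%. It is overstated above that rate and understated below it. PPV is overstated for any f above zero. When f is below s, sensitivity is understated: 86% against 90% at b = 10% and f = 50%.

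**Step 4: what share takes an apparent 90% down to the 80% null?** Solve (10.6 + f·B)/(106 + B) = 0.20, which gives B = 10.6/(f − 0.20). For f = 90%, B = 15.1, or 9.3% of 162. For f = 50%, B = 35.3, or 21.8%.

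**Step 5: link to WP4.** The WP3 activities expect 150 screen positives and give the psychosocial intervention to people who screen positive. WP4 has 150 people with baseline in WP3 and follow-up at 6 and 12 months, without controls. Together these suggest that the screen positives form the cohort, but no eligibility rule is stated. If nobody else changed, brief cases would add (share × their gain) to the mean change. That is 1 point for a 5% share gaining 20% and 18 points for a 30% share gaining 60%, against a 20% target. Neither factor is in the documents, so this shows only how wide the possibilities are.

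**The case against.** - **A reader might infer that accuracy is inflated throughout.** It is not. A tool that passes brief cases over loses apparent sensitivity, and specificity is overstated only if brief cases are flagged more often than non-cases. The assumption that they are flagged as often as ongoing cases is the least favourable one shown. This objection stands.
- **Brief cases may be few.** The Introduction gives a median duration of untreated psychosis of 71 months, and says only that brief psychoses could be more common in such settings, which is not an expectation for this cohort. That argues for a small share. However, the 71 months is tied to the most severe cases reaching services, whereas WP3 finds people in the community and aims at earlier detection, so the share could be larger.
- **A reader might infer that brief cases certainly enter WP4 and bias the result by a known amount.** Entry is an inference, the size is unsupported, and the absence of controls is acknowledged and justified in the article. The planned sensitivity analyses already vary the economic counterfactual, though they do not cover the primary WHOQoL change.
- **Restricting the WP4 primary analysis to ongoing cases would be a poor remedy.** It would shrink the powered sample of 150. If course were judged after baseline, it would select on outcome and could remove people who recovered because of treatment. This also stands, and the fix avoids it.

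None of this removes the mismatch. The article fixes the reference standard itself, so it is not detail left to an analysis plan.

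**Conclusion.** The reference standard and the stated detection target disagree within one paragraph, and nothing else in the article reconciles them. As written, PPV and the powered specificity would be measured against a condition that is not the target. With a 10% brief share, an apparent specificity of 90% corresponds to about 79% to 85% for ongoing psychosis when 50% to 90% of brief cases are flagged. The brief share, the flagging rate and the sensitivity are all assumptions; at a 5% share the loss is about 3 to 6 points. Sensitivity may err the other way.

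For WP4 the documents support only a caution: cases of brief duration may be in the cohort, and their influence on the WHOQoL change should be visible. They do not support a stated amount of bias. The point should be settled before WP3 baseline data are collected.

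**What to change.** 1. Reconcile the two sentences in the Validation study section by stating whether brief psychosis is a target condition.
2. If it is not, record illness duration at the gold-standard interview and classify each person as ongoing, brief or no primary psychosis by a duration rule fixed in advance. The study team should choose the threshold.
3. Make accuracy for ongoing psychosis the main validation result and report any primary psychosis alongside.
4. In WP4, keep the full cohort as primary. Pre-specify a sensitivity analysis of the WHOQoL change and the ICER with and without cases of brief duration at baseline, using only duration recorded at baseline.

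This changes nothing about who receives care. The cost is wording and one coded field from an interview already planned; duration of untreated psychosis is already listed at baseline. Accuracy figures will probably look less favourable. Sensitivity for ongoing psychosis will rest on fewer people, about 146 rather than 162 at a 10% brief share. Keeping 162 would need about 162/(0.604 × 0.9) ≈ 298 screened. One limit remains: a short duration at interview cannot show whether a recent episode will persist, so the brief group should be described as brief to date.
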